**Fig. 1 fig1:**

Trial design and timeline. OASES: Overall Assessment of the Speaker's Experience of Stuttering; SS%:percentage of stuttered syllables; SR:Severity Rating; tDCS: transcranial direct current stimulation.

### Participants and eligibility criteria

2.2

The study population will include adults with moderate-to-severe developmental stuttering who have not received any treatment for at least one month before the intervention. Adults aged between 18 and 50 who stutter will be recruited for this research. The speech-language pathologist will evaluate each participant's stuttering severity to determine if they qualify for enrollment in the study. Inclusion criteria will include a history of developmental stuttering, diagnosis of moderate-to-severe stuttering, right-handedness, age between 18 and 50 years, native speaker of Farsi, no other speech or language disorders other than stuttering, no history of hearing loss, neurological or psychiatric disorders, or seizures, and no intake of any medication that affects brain functions, such as antidepressants. Additionally, individuals who are pregnant, breastfeeding, or have cranial bone defects, cranial or brain metal implants, or skin lesions will be excluded from this study.

### Interventions

2.3

The treatment will have two stages. Stage 1:Speech therapy (Pre-practice or Establishment stage) and Stage 2: transcranial Direct Current Stimulation intervention(Practice stage).

#### Speech therapy (pre-practice or establishment stage)

2.3.1

Both the control and intervention groups will undergo this treatment stage before the start of the tDCS intervention, which will be referred to as the pre-practice(establishment stage). In this stage, the clinician will work with the participant to practice fluency shaping techniques, progressing from simple to complex levels. Each participant will engage in 1–2 h intensive sessions at the clinic to practice fluency-shaping techniques (such as easy onset, airflow, pausing, light consonant contact, and prolongation) at basic levels (phonemes, syllables, words, sentences, and phrases) with the clinician. Subsequently, more complex tasks will be introduced, including reading, monologues, dialogues with the clinician, dialogues and monologues in the presence of strangers, and practicing telephone calls. The goal of this stage will be to ensure that the participant can use fluency shaping techniques in various speech tasks with the clinician in the clinic before entering the combined intervention stage (fluency shaping techniques and brain stimulation). The study participants will be expected to maintain a severity rating (SR) below 2 during these tasks before proceeding to the practice stage. This stage will ensure that clients can use the restructured speech techniques at a simple level with the clinician at the clinic. Then, clients will use these techniques during more complex online practice tasks along with anodal tDCS/Sham tDCS.

#### Transcranial current direct stimulation Intervention(Practice stage)

2.3.2

In this stage of treatment, participants will be randomly allocated to two groups: the intervention group (anodal tDCS) and the control group (sham tDCS). Clients will practice fluency shaping techniques as an online treatment alongside each of ten 20-min tDCS stimulations. Clients will start by reading simple sentences and monologues during the first tDCS session but will eventually progress to more challenging tasks, such as conversing with the clinician, a stranger at the clinic, making telephone calls, and performing dual tasks. The tasks will become hierarchically more complex linguistically and cognitively.

In the tDCS protocol, electrical stimulation will be administered by applying a 2 mA current through two electrodes measuring 5 cm × 7 cm. The process will last for 40 min, with 15-s ramp-up and ramp-down intervals. Each therapy session will last 60 min (20 min of stimulation, 20 min of rest, followed by another 20 min of stimulation). Accordingly, each participant will receive 10 stimulation sessions over 5 therapy sessions conducted on 5 consecutive days. The tDCS will be administered using a Starstim DC stimulator. The tDCS electrodes will consist of conductive rubber encased in sponge pockets, with saline solution used as the electrolyte-based contact medium. It will be essential to saturate the sponges thoroughly with saline. The sponges will need to be properly moistened on all sides without becoming excessively saturated to avoid any dripping. Before placing the electrodes on the scalp, the clinician will examine the skin for any damage or lesions. The same stimulation intensity parameters will be applied for both anodal and sham modes. However, in the sham mode, the device will automatically reduce the intensity after 30 s. An electroencephalogram (EEG) cap will be utilized to determine the stimulation site. The anode electrode will be positioned over the left frontal gyrus (FC5, based on the 10–20 international system) [41], while the cathode electrode will be placed over the right frontopolar region (FP2, according to the same system) [41]. Elastic rubber straps will be used to secure the electrodes in place and prevent any movement.

### Study outcome measures

2.4

#### Primary outcome measures

2.4.1

In this research, the average scores of the percentage of Stuttered Syllables (%SS) obtained from a 10-min unscheduled telephone call will serve as the primary outcome measure. A baseline assessment will be collected one week before the intervention. The identical assessment will be conducted immediately after, and six weeks and three months following the last intervention session (post-treatment assessments). A 10-min unscheduled telephone call with each participant will be conducted by individuals other than the researcher, and this call will be recorded using a call recorder application. Two experienced specialist raters, blinded to the treatment conditions and assessment time points, will independently evaluate and calculate the %SS of all speech samples. The recordings will be coded and screened to ensure anonymity. To calculate the %SS, the total number of syllables associated with unambiguous stuttering for each recorded sample will be counted, divided by the total number of syllables for that sample, and then multiplied by 100 [42]. Stuttering will be characterized as occurrences that involve either (i) repetitions of phonemes, words, or phrases, (ii) prolonged phonemes, or (iii) blocks. It will be important to highlight that, per Riley's definition of stuttering (1994), interjections, silent blocks, and repetitions of whole words or phrases will be considered stuttering if they are articulated abnormally and with tension. Otherwise, they will not meet the criteria for stuttering [43]. The expected mean %SS score at the three post-intervention time points in the anodal tDCS group will be hypothesized to be significantly lower than that found in the sham tDCS group (a diminished %SS score will indicate a less severe form of stuttering). Additionally, no significant difference will be expected between groups at the baseline time point.

#### Secondary outcome measures

2.4.2

Secondary outcome measures will include (i) the overall score for severity rating (SR), which will provide an overall judgment of the stuttering severity in speech, (ii) the overall score for speech naturalness [44], and (iii) the overall score from the OASES questionnaire [45], which will review the psycho-social consequences of stuttering from the viewpoint of the individual who stutters.

##### Severity Rating(SR)

2.4.2.1

Severity Rating is a perceptual evaluation of stuttering, providing an overall judgment of the stuttering severity in speech [44]. In this study, the severity of stuttering will be rated using a 10-point scale, where a score of 0 indicates no stuttering, a score of 1 represents very mild stuttering, and a score of 9 indicates very severe stuttering.

##### Speech naturalness

2.4.2.2

During speech fluency shaping therapy, clients are trained to use an unnatural speech pattern to control their stuttering. Throughout the therapy, they learn to make their speech sound more natural. Essentially, clients need to understand how natural their speech appears to others [46]. In this study, the naturalness of speech will be assessed using a 9-point scale, where a score of 1 indicates the absence of any fluency-shaping techniques, and a score of 9 reflects an exaggerated use of these techniques [44].

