Data will be gathered at four different time points: one week before the intervention, immediately after, 6 weeks after, and 3 months after the intervention. We will examine the effectiveness of anodal tDCS combined with fluency shaping techniques in improving speech fluency by comparing the outcomes of the different treatments. In pre-treatment assessments, we will measure primary and secondary outcome measures before treatment. Pre-treatment assessments will be conducted to evaluate the severity of stuttering before the treatment program begins. The primary outcome measure will be the Percentage of Stuttered Syllables (%SS) obtained from an unscheduled telephone call. Secondary outcome measures will include Severity Rating (SR) and Speech Naturalness obtained from an unscheduled telephone call, and the Overall Assessment of the Speaker's Experience of Stuttering (OASES). After completing these assessments, each participant will engage in treatment sessions. Post-treatment assessments will be conducted immediately after, 6 weeks after, and 3 months after the treatment to evaluate changes in primary and secondary outcome measures and to assess the maintenance and long-term stability of the results.

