### Statistical analysis

2.10

Descriptive statistics will be calculated for demographic and baseline characteristics, in addition to primary and secondary outcomes for all participants engaged in the study. For each participant, summary statistics including mean, standard deviation, median, minimum, and maximum values will be documented for quantitative variables. Frequency tables will be employed to present the data of qualitative variables. Differences among demographic variables will be assessed using Student's t-tests for quantitative variables and chi-square tests for qualitative variables. To evaluate the effect of tDCS on the primary and secondary outcome measures, mixed-model ANOVAs will be used, with group (anodal vs. sham) as the between-subjects factor and time (baseline, immediately post-treatment, 6 weeks, and 3 months) as the within-subjects factor.

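### The speech-naturalness scale grades how much technique is heard, so a low score alone cannot separate natural speech from abandoned technique

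*Protocol article*

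**What the plan says.** All references are to the protocol article.

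- **Speech naturalness (2.4.2.2)** gives the rationale: in this therapy "clients are trained to use an unnatural speech pattern to control their stuttering", then "Throughout the therapy, they learn to make their speech sound more natural", and "clients need to understand how natural their speech appears to others". It then fixes the 9-point scale: "a score of 1 indicates the absence of any fluency-shaping techniques, and a score of 9 reflects an exaggerated use of these techniques". It does not say which end is better.
- **Study design (2.1)** gives the source: "Secondary outcome measures will include Severity Rating (SR) and Speech Naturalness obtained from an unscheduled telephone call". The visits are "one week before the intervention, immediately after, 6 weeks after, and 3 months after the intervention", and speech therapy starts only after the baseline assessment.
- **Participants and eligibility criteria (2.2)** admits adults with moderate-to-severe stuttering and requires no treatment in the preceding month. Earlier therapy is not excluded.
- **Speech therapy (2.3.1)** teaches fluency shaping to both arms before stimulation.
- **Statistical analysis (2.10)**: "To evaluate the effect of tDCS on the primary and secondary outcome measures, mixed-model ANOVAs will be used", with group between subjects and time within subjects. Baseline is one of the four levels of time.
- **Efficacy (2.7)** expects stimulation to make the treatment gains last longer.

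**The concern.** The label and the rationale concern how speech strikes a listener, but the anchors count something else. The two coincide only when audible technique is the sole reason that speech sounds unnatural. That is not so for someone who stutters and uses no technique, because blocked or tense speech can sound unnatural too, and the anchors have no place for it.

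This matters most at follow-up. The trial looks for better maintenance under anodal stimulation. If gains are maintained by continued use of the technique, the better-maintained arm has more audible technique and therefore higher scores. The arm that lets the technique go drifts back towards 1. Anyone who reads lower as more natural would then credit the wrong arm on this outcome. Since the Introduction says that loss of naturalness reduces acceptance of the new speech pattern, the result is likely to be used when the treatment is judged.

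**Working it through.** The plan states no figure for this outcome, so there is none to reproduce. The check applies the stated anchors to the stated schedule and analysis.

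**1. Score by speaker state**

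| State | Technique heard | Score under the anchors | %SS and SR |
|---|---|---|---|
| Baseline, no technique in use | none | 1 | high |
| After training, technique obvious | much | high | low |
| After training, technique made natural | little | low | low |
| Follow-up, technique dropped, relapsed | none | 1 | high |

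The third and fourth rows can share a low score although they are opposite clinical results. Only %SS and SR separate them.

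**2. Change from baseline.** Let b be the baseline score and s a later score, both between 1 and 9. The change s − b lies between 1 − b and 9 − b. With b = 1 the range is 1 − 1 = 0 to 9 − 1 = 8, so that speaker cannot move below baseline. With b > 1, possible because earlier therapy is allowed, a fall of up to b − 1 can occur.

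**3. The group × time contrast.** For one post-treatment visit it is

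(anodal post − anodal baseline) − (sham post − sham baseline).

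If the two baseline means are equal, this reduces to anodal post − sham post. A rise common to both arms cancels here and appears in the time effect. The arm comparison therefore survives a baseline floor. The time effect would be read as lost naturalness.

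**4. Which way the arm comparison points.** Assume that a proportion p of an arm has dropped the technique and scores 1, that the rest average t, and that t is the same in both arms. The arm mean is p × 1 + (1 − p) × t = t − p(t − 1). Then

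anodal − sham = (p_sham − p_anodal) × (t − 1).

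Whenever t > 1 and more of the sham arm has dropped the technique, the anodal arm has the higher score. In the extreme case p_sham = 1 and p_anodal = 0, the difference is t − 1: 1 point if t = 2, 5 points if t = 6, and at most 8 points if t = 9. These values of t and p are illustrations; the article gives none. If anodal stimulation also made the retained technique less audible (a lower t in that arm), the difference would shrink or reverse. The sign of the difference alone does not show which of these happened.

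**The case against.** **Stronger readings to set aside.** A reader might infer that this outcome cannot show improvement, or that the ANOVA can show only worsening. The documents do not support that. Both arms learn the technique, so a score can fall between post-treatment visits (from 6 to 2, say) and the arms can differ. As step 3 shows, the interaction with equal baselines is a post-treatment comparison of arms. Only a fall below baseline, in a speaker already at 1, is ruled out.

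A reader might also infer that baseline is constant at 1. Eligibility bars treatment only in the preceding month, and no baseline distribution is given, so a floor is likely but not certain.

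**Other points in the plan's favour.**

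- The better end of the scale is never stated. That 1 is the natural end is inferred from the outcome's name and from the description of the trained pattern. The article has no rule that would declare a relapsed arm superior on this score.
- The sentence on listeners' impressions is clinical rationale and not a formal endpoint definition. Grading how audible the technique is fits the section's premise that the trained pattern is what sounds unnatural.
- %SS and SR come from the same calls and would reveal relapse. This is the strongest point, and it resolves much of the ambiguity. The article does not, however, say that the measures will be interpreted together.
- The scale is cited to a source that is not at hand, and the article may have shortened fuller anchors. If so, the fault lies in the wording. Even then, the anchors as published do not match the outcome's name.

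These points narrow the concern. They do not remove the mismatch between label and anchors, which is stated in the text and is not a detail left to another document.

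**Conclusion.** The concern holds in a limited form. The anchors measure amount of technique and not naturalness as heard by others. Speech without technique, whether untreated at baseline or relapsed at follow-up, scores at or near the implied natural end, so a low score is not interpretable alone. A rise from baseline after training would read as lost naturalness, although it may only show that the technique was learned. Under the equal-t assumption in step 4, an arm that abandoned the technique could score up to 8 points lower, and so appear more natural, than an arm that kept it.

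This rests on a literal reading of the anchors and on 1 being the natural end. No size can be given for the trial itself, because the article has no expected scores. One secondary outcome is affected; the primary outcome and the sample size are not. It should be corrected before rating begins, since ratings made on these anchors could be replaced only by rating every recording again.

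**What to change.** Settle one of two options before any recording is rated.

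1. **Preferred: re-anchor.** Keep the 9-point listener rating but define 1 as highly natural and 9 as highly unnatural, whatever technique is heard. State that lower is better. The planned ANOVA can then stay as it is for this outcome.
2. **Otherwise: relabel.** Keep the anchors, call the outcome technique use, and state that a lower score is not by itself better. Base the arm comparison on the three post-treatment visits, and interpret it jointly with %SS and SR from the same calls.

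**Cost.** Option 1 changes the rating sheet and may depart from the wording of the cited scale, which weakens comparison with studies that used it. Option 2 gives up the claim to measure naturalness and needs a new outcome name and a changed analysis sentence. Both use the same recordings and raters.

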##### Overall Assessment of the Speaker's experience of Stuttering(OASES) questionnaire

2.4.2.3

In this study, stuttering severity will be assessed using the OASES questionnaire. This tool will evaluate the individual's experience of stuttering across four sections: general information about stuttering, reactions to stuttering, communication in daily situations, and quality of life. Participants will respond to questions using a 5-point scale. The test results will be reported in two values: Impact Scores and Impact Rating, which will reflect the effect and extent of stuttering on the individual's life. The Impact Scores will always range from 20 to 100, and based on this score, the Impact Rating will be classified from mild to severe [45]. In this study, the OASES questionnaire will be completed by participants both before the intervention to assess their comprehensive experience of stuttering and 3 months after the intervention to evaluate the sustainability of treatment effects on their stuttering experience and quality of life.

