The study will focus on adults with moderate-to-severe stuttering. Therefore, stuttering severity will be evaluated before recruitment to confirm enrollment eligibility. The severity of stuttering will be assessed by calculating SS% in unscheduled telephone call for each participant. At the baseline assessment, a 10-min unscheduled telephone call with each participant will be conducted by individuals other than the researcher and this call will be recorded using a call recorder application. Using these data, the primary outcome measure (SS%) will be calculated. Two experienced specialist raters will independently evaluate and calculate the SS% of all speech samples. To assess interrater reliability, Cohen's kappa will be calculated. If the raters agree (intraclass correlation coefficient between 0.8 and 1), the SS% will be reported. However, if there is disagreement (intraclass correlation coefficient below 0.8), a third senior rater will review and evaluate the SS%. The completion of the OASES questionnaire by participants constitutes the final step of the pre-treatment assessments. Following the baseline assessments, the speech therapy sessions will begin. Three time points after the final intervention session (i.e., immediately, six weeks, and three months), each participant will complete post-treatment assessments, which will be identical to the pre-treatment assessments and conducted by the same raters. The trial's design and timeline are depicted in Fig. 1.

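### OASES is scheduled at two times in its own section but at four in the study design, and the four-level time model for secondary outcomes cannot be fitted to two

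*Protocol article*

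**What the plan says.** The secondary outcomes in section 2.4.2 of the protocol article include "iii) the overall score from the OASES questionnaire". Four statements bear on when it is measured and how it is analysed.

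- **Section 2.4.2.3 (OASES).** Participants complete the questionnaire "both before the intervention to assess their comprehensive experience of stuttering and 3 months after the intervention". Each of the two occasions has its own purpose: the first describes the baseline experience of stuttering, the second the durability of the effect.
- **Section 2.1 (Study design), on assessment content.** "The completion of the OASES questionnaire by participants constitutes the final step of the pre-treatment assessments". The text then names the later occasions, "Three time points after the final intervention session (i.e., immediately, six weeks, and three months", and says that "each participant will complete post-treatment assessments, which will be identical to the pre-treatment assessments and conducted by the same raters".
- **Section 2.1, on assessment purpose.** After listing OASES as a secondary outcome, it says the post-treatment assessments run immediately, at 6 weeks and "3 months after the treatment to evaluate changes in primary and secondary outcome measures".
- **Section 2.10 (Statistical analysis).** "To evaluate the effect of tDCS on the primary and secondary outcome measures, mixed-model ANOVAs will be used". The within-subject factor is time with four levels: baseline, immediately post-treatment, 6 weeks and 3 months. No outcome is exempted.

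**The concern.** Someone running the trial cannot follow both sections. Section 2.4.2.3 calls for no OASES immediately after treatment or at 6 weeks; section 2.1 calls for one at each. Someone analysing the trial under section 2.4.2.3 cannot run the model in section 2.10, because two of its four time levels have no OASES data.

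OASES is the only listed outcome that covers quality of life. Section 3 (Discussion) says quality of life will be assessed with it, and both the abstract and the Discussion expect an improvement there.

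Two things are at stake. A questionnaire not completed at an early visit cannot be recovered later. And if the schedule and model stay open until data are in hand, the choice between a change test, a 3-month comparison and a four-time interaction could be made after the results are seen.

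**Working it through.** **Inputs.** There are two groups and N = 62, 31 per group (section 2.9). The number of OASES times is m = 2 (section 2.4.2.3) or m = 4 (sections 2.1 and 2.10). The article gives no figure for OASES to reproduce. Its 62 was derived for %SS and is used here only as a head count.

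**Step 1: the schedules side by side.**

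| Occasion | Section 2.4.2.3 | Section 2.1 | Level in section 2.10 model |
|---|---|---|---|
| Before treatment | yes | yes | yes |
| Immediately after | no | yes | yes |
| 6 weeks | no | yes | yes |
| 3 months | yes | yes | yes |

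**Step 2: can the stated model be fitted?** A model with 2 groups and 4 times has 2 × 4 = 8 cell means. With data at two times only, 2 × 2 = 4 cells are filled and 4 are empty. The 8-column cell-means design then has rank 4 (confirmed numerically), so four of the eight means, and with them the full time effect and interaction, are not estimable.

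**Step 3: what remains.** The interaction has (m − 1)(2 − 1) numerator and (N − 2)(m − 1) denominator degrees of freedom.

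- Four times: 3 and 60 × 3 = 180.
- Two times: 1 and 60 × 1 = 60.

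The two-time interaction F equals the squared t statistic comparing change from baseline between groups. On one simulated data set of 62 participants both came to 1.373. This is a valid test, but of a different hypothesis from the 3-df interaction.

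**Step 4: ANCOVA against the change test, if two times are kept.** Assume equal variance σ² at both times and baseline-to-3-month correlation ρ. The article gives no ρ for OASES, so a range is shown.

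- Change score variance: 2(1 − ρ)σ².
- ANCOVA residual variance: (1 − ρ²)σ².
- Ratio: (1 − ρ²) / [2(1 − ρ)] = (1 + ρ)/2.

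| Assumed ρ | Ratio | Reduction |
|---|---|---|
| 0.3 | 0.65 | 35% |
| 0.5 | 0.75 | 25% |
| 0.7 | 0.85 | 15% |
| 0.9 | 0.95 | 5% |

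The one degree of freedom spent on the covariate is ignored. These figures bear on the choice of repair; the contradiction does not depend on them.

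**Step 5: questionnaire count.** Two times: 62 × 2 = 124. Four times: 62 × 4 = 248. Difference: 124, with no dropout.

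**The case against.** The strongest reply is that section 2.4.2.3 is the specific rule for this instrument and the other statements are general. In section 2.1, the sentence on primary and secondary measures can be read collectively, without meaning that each is taken at each visit. The reference to the same raters suits recorded speech samples better than a self-completed questionnaire. The abstract ties the assessment times explicitly only to the primary outcome. Fig. 1, whose legend names OASES, is not shown and may give the schedule. An article may also leave the time levels of each secondary analysis to a fuller plan.

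Part of this stands. The collective reading is possible, so that sentence is weak support alone. But section 2.1 names OASES as the last step of the pre-treatment assessments and then calls the later assessments identical, so the plain reading includes OASES at all three. A figure could favour one schedule but could not make the two sections agree. Nor is the model a detail left out: section 2.10 states its four levels and applies them to the secondary outcomes without exception.

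It also stands that the same method works with two levels. A reader might infer that OASES cannot be analysed at all, or that half its data would be missing. The documents support neither: a 2 × 2 analysis is estimable, and under section 2.4.2.3 the two intermediate questionnaires were never planned. Nor is inconsistency between sites a worry, since section 2.1 names a single clinic and laboratory.

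**Conclusion.** The current text contradicts itself on the OASES schedule (two times against four), and under the two-time schedule the four-level analysis in section 2.10 cannot be carried out for this outcome. This rests on the plain reading of the text and on counting cells; the assumed correlations play no part in it. Fig. 1 could not be checked.

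The weight is moderate. A reader might take the conflict as a threat to the trial's main result, but the primary outcome is %SS and section 2.9 bases the sample size on %SS alone, so neither is affected. The quality-of-life statements in the abstract and Discussion are expectations, not planned inferential claims; what suffers is the pre-specification of the one outcome that would inform them.

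**What to change.** Settle one OASES schedule before data collection and state it identically in sections 2.1 and 2.4.2.3, and in Fig. 1 if that differs. Either resolution is workable.

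- **Two times.** In section 2.1, exempt OASES from the assessments repeated immediately and at 6 weeks. In section 2.10, take OASES out of the four-level model and add one sentence: the 3-month Impact Score is compared between groups by ANCOVA with the baseline Impact Score as covariate. A 2 × 2 ANOVA would also be valid; ANCOVA is suggested for its smaller residual variance (35% to 5% lower for assumed ρ of 0.3 to 0.9). This is a text change and needs no extra data.
- **Four times.** Correct section 2.4.2.3 to list all four occasions. Section 2.10 then works for OASES as written. The cost is up to 124 more questionnaires than section 2.4.2.3 plans for 62 participants.
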